#### Randomization and allocation concealment

Individuals will be randomly assigned in the four groups (red, blue, green, and black) through a computer-generated random number list. A statistician will assign the individuals into four groups by a computer-generated list and would then assign color codes (red, blue, green, black) without knowing which color belongs to which group. This randomization will be stratified on gender and age (10–13 years, 14-19years, 20–40 years old) and adjusted for serum zinc, BMI, zinc deficiency and HbA1C.

An independent consultant from an international University (University of Sydney) would be responsible for assigning the three intervention and control groups to each color group and will not be involved in the trial, including recruitment, implementation, or evaluation. The consultant would be responsible for generating and safeguarding the code and would be the only person communicating with the flour mill (Shoaib Corporation) and nutrition laboratory to ensure that the correct flour is being milled and packed in the right color bag for each batch. The consultant will break the code when the final data is collected and analyzed.

This flour mill site (Saleh Pat) is located about 500km from the trial site and the flour would be transported fortnightly to the field site. Shoaib Corporation has set up a separate local mill (chakki) for the study and has the warehouse where the two different varieties of wheat are being stored. They would be responsible to mill, fortify (ZnO - 80mg/kg) and pack high zinc, fortified, and low zinc wheat/flour in 40kgs polypropylene sacks, corresponding to a specific color. To ensure accuracy, fortnightly samples of color-coded products will be sent to the laboratory and the results will be shared with the consultant for confirmation.

#### Blinding

Participants, study personnel, and the outcome assessors will be kept unaware of the study groups. All aspects of the study, from randomization to implementation, data collection, and analysis, will be conducted using color codes assigned by an independent statistician. Color codes will be applied to wheat bags, ensuring packing, storage, and transportation in appropriately colored containers. Once participants are randomized, they will receive a laminated ID card with their photo, with the card’s color indicating their assigned group to ensure that participants do not attempt to swap groups. A study kitchen is set up at the field site and has separate color-coded tandoors (ovens) for each group and would also have separate teams preparing these flatbreads who will wear color-coded aprons. Lunchboxes containing flatbread and curry will also be color-coded and packed at the study kitchen and transported to respective schools/colleges and designated community spaces.

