### Study design

This would be a four arm individually randomized, triple-blind trial conducted in a rural district of Pakistan. The study will adhere to the guidelines outlined in the Consolidated Standards of Reporting Trials (CONSORT) for RCTs [22]. The trial is registered at clinicaltrials.gov with number NCT06092515 [23]. Fig 1 highlights the SPIRIT schedule of the trial (S1 Checklist).

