**Fig 2 pone.0304462.g002:**
[figure not shown]
Study groups.

Group 1: will receive fermented high zinc agronomically biofortified wheat (>35mg/kg) flour flatbread.Group 2: will receive unfermented high zinc agronomically biofortified wheat (>35mg/kg) flour flatbread.Group 3: will receive fortified (post-harvest) whole wheat (80mg/kg) flour flatbread.Group 4: will receive low zinc conventional whole (20–25 mg/kg) wheat flour flatbread.

The intervention duration will be six months, and participants will be provided with the respective ‘flatbread’ with a vegetable curry or pulse (*daal*) meal once a day for six days a week for six months This meal would be distributed at schools/colleges or community spaces during break or after the school is over.

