### Intervention delivery

#### Flatbread preparation, and delivery

The flatbread and the vegetable/pulses curry will be prepared in the study kitchen established at the study site and professional catering staff will be hired to prepare food following standard guidelines. Four color-coded tandoor ovens will be set up, and the designated kitchen staff for each group will wear color-matched uniforms. The regular menu will feature flatbreads with a choice of vegetable curry or pulses, designed weekly and prepared in the study kitchen to ensure consistency.

High zinc fortified flour and low zinc wheat flour will be mixed separately with water, salt, oil in their respective color-coded utensils. The ingredients will be kneaded by hand to form soft dough. The dough will then be covered with a muslin cloth and the resting time of the dough will be kept identical for each of the produced flour portions (30 min) (Table 1) For fermented flour, we will add 3.5g yeast /kg of flour and let the dough rest for 2hrs at 30 degrees Celsius.

**Table 1 pone.0304462.t001:** Ingredients for flatbread.

Ingredients	Unit	Quantity	
		Fermented	Unfermented
Wheat flour	g	1000	1000
Active dry yeast	g	3.50	-
Iodized Salt	g	4	4
Ghee/cooking oil	g	30	30
Water for kneading the dough	ml	300	300
One ball of dough	g (±5g)	125.00	
Weight of one ready cooked flatbread	g (±5g)	100.00	

Each ball will be weighed on a weighing machine to ensure that each ball has a weight of 120 grams. It will be transferred to a baking tray or round cushion lined and these will be used to place the flatbreads inside separate tandoors for each group. To allow for proper rising, flatbreads will be spaced adequately inside the tandoor. Prepared flatbreads will be packed in color coded lunch boxes and each box will have two flatbreads (each flatbread divided in four equal parts) and curry under supervision. These boxes will then be transported to the targeted schools/colleges/community space and packing will ensure that the freshness of flatbread is maintained.

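### The unqualified triple-blind claim cannot hold for the Group 1 kitchen team, and Group 1 carries the same exposed colour through to the analysis

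*Protocol article*

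**What the plan says.** Study design: "This would be a four arm individually randomized, triple-blind trial conducted in a rural district of Pakistan". The Blinding section specifies who is blind: "Participants, study personnel, and the outcome assessors will be kept unaware of the study groups". No one is exempted.

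The means of blinding is a set of four colours: "All aspects of the study, from randomization to implementation, data collection, and analysis, will be conducted using color codes". The colour is on the flour bags, the lunchboxes and each participant's ID card. The study kitchen "has separate color-coded tandoors (ovens) for each group and would also have separate teams preparing these flatbreads who will wear color-coded aprons".

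The list of groups under Fig 2 has a single fermented arm: "Group 1: will receive fermented high zinc agronomically biofortified wheat (>35mg/kg) flour flatbread". Groups 2 to 4 have no fermentation step. The section on flatbread preparation gives the resulting difference in handling: "For fermented flour, we will add 3.5g yeast /kg of flour and let the dough rest for 2hrs at 30 degrees Celsius". The other doughs get no yeast (Table 1) and a 30-minute rest.

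The section on randomization and allocation concealment adds safeguards. The allocating statistician does not know what the colours mean. An independent consultant holds the code and is the only contact with the mill and the nutrition laboratory. As a check on the flour, "fortnightly samples of color-coded products will be sent to the laboratory", and the results go to that consultant.

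**The concern.** Colour coding masks a difference that cannot be seen, such as the zinc content of flour. It does not mask a difference in how the food is made. Whoever adds yeast to one colour's dough and leaves it to rise knows which colour is the fermented arm, and no other arm is fermented.

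Because one label runs from the oven to the analysis file, that knowledge is not confined to the kitchen in principle. Anyone who learns it can read the allocation of every Group 1 participant from a card, a lunchbox or a dataset.

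At stake are the measures that knowledge of the arm can influence: fortnightly reported diarrhoea and respiratory infection, 24-hour dietary recall, and the daily record of bread eaten, made by the study team at the meals where staff also hand out extra bread on request. The analysis is exposed too, because the Trial analysis section leaves choices to be made on the data: covariates picked for baseline imbalance, and a backward procedure for the regression model. The Discussion names the added effect of fermentation as something the trial explores. Groups 1 and 2 isolate that effect, and fermentation is the feature that can be noticed.

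**Working it through.** The article gives no figure on this point to reproduce. The check sets its statements side by side and counts what each piece of knowledge reveals.

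**Step 1. Kitchen team.** One arm is fermented (list under Fig 2). Its dough is handled visibly differently (flatbread preparation, Table 1): 3.5 g yeast per kg and 2 h of rest, against no yeast and 30 min. Each colour has its own team and oven (Blinding). The team for that colour therefore has to be told to ferment. If kitchen staff are study personnel, the Blinding statement is false for them on the article's own procedures.

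**Step 2. What each fact reveals.** Four colours map to four groups in 4! = 24 ways.

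| Known | Maps left | Revealed |
|---|---|---|
| Nothing | 24 | Nothing |
| Which colour is yeasted | 3! = 6 | Group 1, in all 6 maps |
| Flour zinc by colour (two colours >35, one 80, one 20–25 mg/kg) | 2! × 1 × 1 = 2 | Groups 3 and 4; Groups 1 and 2 cannot be told apart |
| Both | 1 | The whole code |

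Fermentation therefore identifies Group 1. The flour assay does not, because Groups 1 and 2 use the same high-zinc wheat.

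**Step 3. Reach of the label.** The sample size section plans 250 per group, so one known colour identifies 250/1000 = 25% of participants. Of the 4 × 3 / 2 = 6 pairwise contrasts, 3 involve Group 1. Of the 3 contrasts with the conventional flour in the stated objective, 1 does.

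**Step 4. Participants.** The Introduction says that common naan is fermented and that most households eat unfermented bread, so both kinds are known locally. The Product development section reports that the sensory panel found the products acceptable; it does not say they were indistinguishable. The Discussion's remark that zinc leaves sensory characteristics unchanged supports masking among Groups 2 to 4 but says nothing about leavening. Recognition is likely but not stated.

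**Step 5. Outcomes exposed.** All primary outcomes are laboratory measures, and blood samples carry barcodes (Biochemical sample collection). BMI, blood pressure, anaemia and red-cell fatty acids are measured. Morbidity and dietary intake are reported, and bread intake is recorded by staff at the meal.

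**The case against.** The strongest reply is that the safeguards are real and the breach is narrow. The catering staff are hired separately, their training is described apart from that of the research staff, and they are given no part in outcome assessment. They receive coloured sacks that do not show zinc content. Groups eat in separate rooms, which limits side-by-side comparison. Leavened bread is not foreign to the area. Noticing it reveals the arm only to someone who knows that exactly one arm is fermented, and what participants are told is not shown. The statistician who allocates does not know the colours' meaning, and nothing puts the analyst in contact with the kitchen.

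Most of this stands, and it rules out three stronger readings that a reader might infer:

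- **That the flour assay exposes Group 1.** It cannot, as Step 2 shows. It separates Groups 3 and 4 from the high-zinc pair. This is a minor route, since the results go to the consultant, who already holds the code, and blood tubes are barcoded.
- **That blinding has failed for every Group 1 participant.** The documents make this plausible, not certain.
- **That the analyst is unblinded.** That needs a leak. The article leaves a leak possible by keeping the kitchen's colours in the analysis, but it does not describe one.

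What the reply does not remove is the universal wording. Kitchen staff work for the study and are trained by it, and the Blinding section itself includes their ovens and aprons among the blinding measures. A fuller protocol could add detail, but it could not make the Group 1 team unaware that its dough is fermented.

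**Conclusion.** The point holds in a limited form. The claim that all study personnel are unaware of the groups is contradicted by the article's own procedures for one team. This rests on counting kitchen staff as study personnel, which is the natural reading. For Group 1 participants and the staff serving them, blinding is doubtful. For analysts it depends on a label whose Group 1 meaning is known in the kitchen, with no recoding step described.

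Up to 250 of 1000 participants can be identified from one colour. The effect on the primary laboratory outcomes should be small. For reported morbidity, 24-hour recall, recorded bread intake and analysis choices made on the data, contrasts involving Group 1 should not be presented as blinded without qualification. The size of any bias cannot be calculated from the document.

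**What to change.** 1. Qualify the Study design and Blinding statements: the Group 1 kitchen team is not blind to fermentation, and Group 1 participants and meal staff may not be.
2. Have the existing independent consultant issue the analysis dataset with arm codes unrelated to the kitchen colours, and keep the link until the analysis is complete.
3. Instruct field staff to keep ID card colour out of sight at morbidity and dietary interviews where feasible.
4. State in advance that self-reported outcomes in contrasts involving Group 1 will be interpreted as possibly unblinded.

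None of this alters the bread, the randomization or the staffing, so it remains possible although enrolment began in August 2023. The cost is a small relabelling task for the consultant, one field instruction, and giving up the unqualified triple-blind label.

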#### Procedure of serving flatbread/curry in schools

Field staff will deliver the respective lunchbox to the specific group in each school. The adolescents in different groups in a single school/college would be segregated and seated in separate marked rooms. The lunch boxes would be delivered after matching participants’ specific IDs on the box with the student badges. The staff will also have extra flatbreads in color-coded bags and would give to individuals who would demand for more. The study team will record the amount of flatbread consumed by each participant for each day and data recorded electronically on an android app. Research staff and teachers will ensure each participant receives their designated lunch, record food consumption, and maintain order, ensuring that food is not being shared or taken home.

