### Baseline, midline, and endline data collection

Participants will undergo assessments at baseline and endline, where we will gather data on socio-demographic factors, dietary intake via 24-hour dietary recall, anthropometric measurements (weight, height, MUAC, waist circumference), blood pressure measurements, and blood samples will be collected for biochemical analysis, including serum zinc levels, FBS, HbA1C, and insulin at both time points. Lipid profile and RBC membrane fatty acids will be assessed only at the endline. At midline, we will conduct 24-hour dietary recalls, measure serum zinc and HbA1C for a subset from each group. The data for morbidity (diarrhea and ARI) will be collected fortnightly for the entire duration of the intervention.

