#### Morbidity

Incidence and duration of diarrheal episodes and respiratory tract infections will be recorded every two weeks throughout the study.

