### Ethical considerations

This study will secure ethical approval from both the Aga Khan University Ethical Review Committee (ERC) and the National Bioethics Committee (NBC), Pakistan (S1 Checklist). We will consistently uphold ethical principles, ensuring autonomy, anonymity, confidentiality, and equity throughout the study. Informed consent will be obtained from all eligible participants, with parental or caregiver consent for those under 18, alongside assent. Collaborations with the Education and Health departments of the district will be closely maintained. Participants diagnosed with T2DM and other issues will be referred to appropriate health facilities. Any adverse event due to the intervention (though unlikely) will be taken care by the study. We will conduct regular community engagement events and information sessions during the intervention to address concerns and encourage continued participation. Participants will be free to withdraw from the trial at any point. Ethical conduct with trial participants, especially children, will adhere to UNICEF’s ethical guidelines [45]. These principles emphasize the utmost respect for every child’s dignity and rights, ensuring privacy, confidentiality, and participation in decisions that affect them. All blood samples and other reports will be shared with the participants. Any changes to the protocol will be informed to the ethical review committee.

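### Each arm has its own flatbread team and oven with no rotation described, so a team-level hygiene effect on diarrhoea cannot be told apart from a flour effect

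*Protocol article*

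**What the plan says.** Randomisation is individual, 1:1:1:1, with 250 participants per arm (Study design; Sample size calculation). Delivery of the bread is organised by arm:

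- Blinding: the study kitchen has "separate color-coded tandoors (ovens) for each group and would also have separate teams preparing these flatbreads who will wear color-coded aprons".
- Flatbread preparation, and delivery: "the designated kitchen staff for each group will wear color-matched uniforms". Dough is kneaded by hand, and the finished breads are divided into quarters and boxed by colour under supervision.
- Same section, on the shared part of the meal: "The flatbread and the vegetable/pulses curry will be prepared in the study kitchen established at the study site". No separate cooking of the curry by arm is described.
- Procedure of serving flatbread/curry in schools: "The adolescents in different groups in a single school/college would be segregated and seated in separate marked rooms".
- Intervention: the flatbread comes with a curry or pulse "meal once a day for six days a week for six months".

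Morbidity is part of the aim stated in the Introduction, and diarrhoea and ARI are listed as secondary outcomes. On collection, the article says "The data for morbidity (diarrhea and ARI) will be collected fortnightly for the entire duration of the intervention". The Trial analysis section gives a mixed model with time and group as fixed effects and a random intercept per student. It has no term for team, oven, room or site.

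**The concern.** Individual randomisation balances the participants, but it does not balance what is attached to an arm afterwards. One team handles all the flatbread of one colour, so anything about that team (an infected handler, poorer hand hygiene, a contaminated work surface) reaches that arm and no other. Diarrhoea is the outcome in this trial most exposed to food handling. It is also one on which zinc may act: the Introduction cites fewer diarrhoeal episodes with supplementation in children.

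An excess of diarrhoea in one colour could therefore be reported as harm from fortified or fermented bread when it came from the kitchen. A real effect of the bread could equally be put down to hygiene, and an apparent benefit of zinc could reflect a cleaner team.

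**Working it through.** The article states no rate, effect size or power for diarrhoea, so there is no figure to reproduce. The first step is structural; the other three are illustrations on assumed rates.

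**1. Aliasing.** There are four arms and four flatbread teams, matched one to one. Once the arm effect is fitted, no degrees of freedom remain for team. The student-level random intercept does not help, and neither would a team term, because it would be collinear with arm. If one team serves one colour throughout, this cannot be repaired at analysis.

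**2. One incident, comparing episode counts.** Two arms, Poisson counts, no flour effect. Background B is equal in both arms, and E extra cases fall in one:

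z = E / √(2B + E)

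Assumed B is 50, 125 or 250 episodes per arm over six months (0.2, 0.5 or 1.0 per person among 250). Assumed E is 25 (10% of 250) or 50 (20% of 250).

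| E | B = 50 | B = 125 | B = 250 |
|---|---|---|---|
| 25 | 25/√125 = 2.24, p = 0.025 | 25/√275 = 1.51, p = 0.13 | 25/√525 = 1.09, p = 0.28 |
| 50 | 50/√150 = 4.08, p < 0.001 | 50/√300 = 2.89, p = 0.004 | 50/√550 = 2.13, p = 0.033 |

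These are unadjusted two-sided p-values for one pair of arms.

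**3. The same question by participants with any diarrhoea.** Take 225 per arm (250 × 0.9, the article's 10% dropout), baseline risk p₀ and attack rate a in one arm, so that p₁ = p₀ + (1 − p₀)a. The chance of p < 0.05 in a two-sided pairwise test with no flour effect is:

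| Assumed baseline risk | a = 5% | a = 10% | a = 20% |
|---|---|---|---|
| 10% | 31% | 78% | about 100% |
| 20% | 17% | 51% | 97% |
| 40% | 9% | 25% | 73% |

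**4. No outbreak, only persistent team differences.** With one team per arm, the design effect is 1 + (225 − 1) × ICC. The true type I error of a naive 5% pairwise test is 2 × [1 − Φ(1.96/√design effect)]:

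| Assumed team-level ICC | Design effect | Type I error |
|---|---|---|
| 0.001 | 1.22 | 7.6% |
| 0.005 | 2.12 | 17.8% |
| 0.01 | 3.24 | 27.6% |

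The results depend strongly on the assumed inputs. A small incident against a high background would often go unnoticed; a moderate one against a low background would usually look like a treatment effect.

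**The case against.** Several stronger readings are tempting, and the article does not support them.

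- **A reader might infer that teams are fixed for six months.** The article speaks of separate teams and designated staff; rotation is neither described nor excluded. A staff rota is operating detail that a condensed article may leave to the full protocol.
- **A reader might infer that each arm eats in one room, so that contagion stays within the arm.** Rooms are separated within each school or college, so an arm has several, and this is stated for adolescents only. No arm-specific rooms are described for community spaces. The arms share schools and community outside the meal, so a contagious illness, ARI above all, has no reason to stay in one colour.
- **A reader might infer that any food-borne event falls on one arm.** The curry comes from the same study kitchen with no arm-specific cooking described, so a curry-borne incident could reach all four.
- **A reader might call diarrhoea and ARI the only harm data.** They are secondary outcomes. Blood pressure, anthropometry and blood markers are also measured, and on adverse events the article says "Any adverse event due to the intervention (though unlikely) will be taken care by the study". Their recording may be set out in the full protocol.

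There are also safeguards: professional caterers following standard guidelines, supervised packing, hygiene training for kitchen staff and field-supervisor spot checks. They lower the chance of an incident but do not remove the aliasing.

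On size, every rate is assumed, and the Trial analysis section plans post-hoc tests adjusted for multiple comparisons. If that were Bonferroni over six pairs (0.05/6 = 0.0083, an assumption), none of the 25-case scenarios would be significant, and of the 50-case scenarios the one at p = 0.033 would drop out.

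Finally, colour-dedicated teams guard against flour mix-ups and so protect the serum zinc comparison. That is a good reason for the arrangement.

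These points narrow the concern to flatbread handling and diarrhoea. They do not answer it there.

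**Conclusion.** The concern holds in a limited form. With one flatbread team and one tandoor per arm, and no rotation described, flatbread-team hygiene is aliased with flour for diarrhoea. The aliasing follows from the article's own text, on the assumption that teams stay with their colour. It applies only weakly to ARI and is not shown to touch any primary outcome.

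How much it matters cannot be fixed from the article. Across the assumed backgrounds, one incident adding 25 cases gives unadjusted p from 0.025 to 0.28, and one adding 50 gives p from below 0.001 to 0.033, with no flour effect. Adjustment for multiple comparisons would make such false signals rarer, but it would not show which of the two causes produced a signal that remained.

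A reader might infer that the Trial analysis model is at fault for lacking a team or room term. It is not: with one team per arm, no such term could be estimated. The limit lies in the delivery, so what can change is the incident record, the sensitivity analysis and the strength of the diarrhoea conclusion.

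**What to change.** 1. **Log incidents.** Record food-safety incidents and clusters of illness by colour, team, site and date in the existing app, for the flatbread and the curry.
2. **Pre-specify one sensitivity analysis for diarrhoea.** Repeat the arm comparison without the affected fortnights, dropping them for all four arms so that the same calendar time is compared. Define an affected fortnight before the colour code is broken, and where possible from kitchen evidence: a rule based on diarrhoea counts alone could remove a true flour effect. This handles recognised incidents only, not a persistent difference between teams.
3. **Limit the conclusion.** State that between-arm differences in diarrhoea cannot be separated from kitchen-team effects. Enrolment began in August 2023, so this also covers time already elapsed.

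The cost is about two extra app fields and one extra analysis.

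**Optional: rotate the teams** across colours, with flour, utensils and ovens kept colour-specific. Rotation would average out persistent team differences. It would not remove a single incident, which would still fall on whichever colour the team was serving, and a contaminated flour batch would stay with its colour. It must be weighed against the risk of flour mix-ups, which bear on serum zinc, and against more staff learning which colours are fermented. Leaving the teams as they are is defensible if items 1 to 3 are done.
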